### Study hypothesis and principal comparisons

The primary outcome of the study is to investigate if the addition of FDP (250mg/kg loading dose over 20 minutes followed by 6mg/kg/hr for 24 hours) to routine treatment will completely reverse serious arrhythmias within two hours. The study will also investigate the effect of FDP on the presence of abnormal rhythms and serum potassium and other electrolytes over 24 hours.

### Statistical Analysis

The Primary outcome (proportion with reversion to sinus rhythm) will be compared with the chi-squared test. Kaplan Meier curves will be constructed to demonstrate the cumulative reversion to sinus rhythm over time. A Cox proportional hazard model will be used to test the overall difference in reversion to sinus rhythm between treatments adjusted for baseline variables as necessary. A longitudinal statistical technique known as Generalised Estimating Equation (GEE) will be used to analyze changes in electrolytes (e.g. potassium) over time.

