### Randomisation

Randomisation is done using purpose designed computer software. The random sequence and allocation are concealed prior to randomisation. The program will randomise eligible patients in a 1:1 ratio. The allocation sequences are generated and encrypted independently by an IT consultant who has no role in patient recruitment, treatment and assessment.

The randomization will be performed by study pharmacists centrally. If a patient meets the inclusion criteria and gives consent, clinical research assistants will call the pharmacist with details such as name, hospital number and weight of the patients. Then the pharmacist will randomise the patients and prepare the placebo or active treatments for the study team. The allocation will only be known by the pharmacists who will have no other role in patient management and data collection. Intention-to-Treat analysis will be applied. That is, the analysis will include all randomised patients in the groups to which they were assigned, regardless of non-compliance, protocol deviations, withdrawal, and anything that happens thereafter [17]

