### Sample size

We are planning to recruit 240 symptomatic patients with yellow oleander poisoning admitted to Teaching Hospital, Kurunegala and National Hospital Sri Lanka, Colombo. In the study by Eddleston M et al [18], 2/32 (6.25%, 95% CI 1% - 19%) patients reverted to sinus rhythm spontaneously after 2 hours. Second degree and third degree heart block are markers of toxicity but may not be strong predictors of death (which may be due to myocardial toxicity rather than atrio-ventricular conduction block). Reversion to sinus rhythm is more likely with less severe second degree block. We would ideally have a sample size that ensured a significant number of third degree blocks which are less likely to revert spontaneously so that the effect of treatment in this sub-group can be seen. However, the proportions of the different grades of block are not well quantified and thus precise estimates of power in sub-groups are not possible.

We expect up to 15% spontaneous reversion by two hours and believe a 40% reversion in the active treatment arm would be clinically significant and likely to provide strong evidence that this would translate to a mortality benefit. This would require just 60 patients in each arm (α = 0.05, β = 0.8, missing data/dropout 10%). To increase the likelihood of recruiting enough patients with 3^rd ^degree heart block to see if the effect is observed in the most severely poisoned patients, and to account for possible differences between centres we intend to do a study of 120 patients in each arm.

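### The primary chi-squared test uses neither block grade nor centre, although the sample-size reasoning relies on both; a stratified test would be a modest, nearly free gain

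*Protocol article*

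**What the plan says.** **Statistical Analysis.** "The Primary outcome (proportion with reversion to sinus rhythm) will be compared with the chi-squared test". No stratification or covariate is named for this test. A Cox model for reversion is also planned, adjusted for baseline variables where needed, but the variables are not named.

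**Sample size, block grade.** "Reversion to sinus rhythm is more likely with less severe second degree block". The section adds that third degree block reverts spontaneously less often, and that the mix of grades is poorly known.

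**Sample size, planned effect.** "We expect up to 15% spontaneous reversion by two hours", and "a 40% reversion in the active treatment arm would be clinically significant". On that basis: "This would require just 60 patients in each arm".

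**Sample size, enlargement.** Two reasons are given for doubling the trial. One is to recruit enough third degree block to see the effect there. The other is centre: "to account for possible differences between centres we intend to do a study of 120 patients in each arm".

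**Randomisation.** Allocation is central and computerised: "The program will randomise eligible patients in a 1:1 ratio". The section neither states nor rules out stratification.

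**The concern.** The protocol identifies a baseline factor that predicts its own primary outcome, and a second factor, centre, that it considers worth guarding against. The test it then fixes uses neither. Doubling the number of patients in a pooled two-by-two comparison makes the overall difference more precise. It does not remove variation between hospitals, and it does not correct for one arm receiving more third degree block by chance.

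At stake are some power, a primary estimate that moves with any chance imbalance in block grade, and a mismatch between a stated reason for the larger trial and its main analysis. The Cox model does not close the gap, because it does not replace the primary test and its covariates are left open.

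**Working it through.** **1. The plan's own figure.** Inputs from Sample size: control 15%, active 40%, and "α = 0.05, β = 0.8, missing data/dropout 10"%. The 0.8 is read as power, and a two-sided test is assumed because sidedness is not given.

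n per arm = [1.96·√(2·0.275·0.725) + 0.842·√(0.15·0.85 + 0.40·0.60)]² / 0.25² = (1.238 + 0.510)² / 0.0625 ≈ 49. Then 49/0.9 ≈ 55.

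The stated 60 per arm leaves 60 × 0.9 = 54 evaluable. That gives 83.9% power by chi-squared and 78.8% by Fisher's exact test, so 60 is reproduced to within 2 points of 80% by the exact test and is slightly generous for the test named.

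**2. Power of the planned test at full size.** 120 × 0.9 = 108 evaluable per arm. Power = Φ[(0.25·√108 − 1.238)/0.606] = Φ(2.24) = 98.8%. Little power is left to gain at the planned effect.

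**3. How far block grade could drift by chance.** This step assumes simple randomisation, which the article does not state. With an assumed 40% third degree share, the SD of the difference between arms is √(2·0.4·0.6/n).
- n = 120: SD 0.063, so a gap of 10 points or more has probability about 11%.
- n = 60: SD 0.089, probability about 26%.

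With assumed control reversion of 25% in less severe rhythms and 5% in third degree block, a 10-point gap shifts the treatment difference by 0.10 × (25 − 5) = 2 points, against a design difference of 25.

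**4. Pooled chi-squared v Cochran-Mantel-Haenszel (CMH).** This used simulation with 40,000 runs per scenario, simple randomisation, two strata (third degree v the rest) and a common odds ratio. The documents give no stratum rates or shares, so these are assumptions: third degree share 20–50%; control reversion in third degree 2–10%; the rest set so that the overall control rate is 15%. For example, with a 35% share and 5% reversion, the rest is (0.15 − 0.35·0.05)/0.65 = 20.4%.

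Power, chi-squared → CMH:

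| Third degree share; control rates (third degree / rest) | 108 per arm, 15% v 40% | 108 per arm, 15% v 30% | 54 per arm, 15% v 40% |
|---|---|---|---|
| 20%; 10% / 16.3% | 98.8 → 98.8 | 76.4 → 76.2 | 84.2 → 84.5 |
| 35%; 5% / 20.4% | 98.9 → 99.3 | 75.8 → 78.1 | 84.0 → 86.6 |
| 50%; 5% / 25.0% | 98.9 → 99.5 | 76.2 → 80.6 | 84.6 → 88.8 |
| 50%; 2% / 28.0% | 98.9 → 99.8 | 76.4 → 84.9 | 84.6 → 92.8 |

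The last row is the case where grade is very strongly prognostic. With no treatment effect and 108 per arm, rejection was 5.1–5.5% for chi-squared and 4.9–5.3% for CMH.

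**5. The proposed test itself.** A six-stratum CMH (three rhythm groups by two hospitals) was also simulated. It kept type I error at about 5% and lost no power against the pooled test.

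**The case against.** The strongest reply is that an unadjusted chi-squared test is a valid primary test in a randomised trial, and that at the planned effect and size stratification buys less than 1 point of power. Both statements are correct. The 54-per-arm column uses α = 0.05, whereas the interim look at 60 per arm uses 0.001, so it does not describe the stopping decision. Adjustment is also already foreseen in the Cox model.

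A reader might infer more than the documents support:
- **That randomisation is unstratified.** The article says only 1:1, and a condensed article may leave stratification to the full protocol. This is not a finding. The analysis point does not depend on it: in the simulations, stratified allocation followed by a pooled chi-squared test gave type I error of 3.4–5.1%, at times conservative, while CMH stayed near 5%.
- **That centre is a stated driver of reversion.** The text speaks only of possible differences.
- **That the enlargement fails the third degree aim.** A larger trial does recruit more such patients. What it does not do is account for centre or for imbalance.
- **That the loss of power is large.** Rates of 45%/5% on placebo and 65%/15% on FDP in equal strata give 66% v 77% at 108 per arm. They imply (45 + 5)/2 = 25% reversion on placebo, above the protocol's ceiling of 15%.

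What remains is that the article states a choice of primary test that sits poorly with its own reasoning, and that a better-matched test is available at almost no cost.

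**Conclusion.** The point holds as a modest improvement in efficiency and robustness. The primary inference as planned is not wrong or biased. The gain is under 1 point of power at 15% v 40% with 108 evaluable per arm. If the true FDP rate is nearer 30%, or at 54 per arm, it is about 0 to 4 points when third degree control reversion is 5–10%. It reaches about 8 points if that rate is 2% and half the patients have third degree block.

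These gains rest on assumed grade shares and stratum rates, a common odds ratio and two strata. The mismatch rests on the text alone: block grade is said to predict reversion, centre is given as a reason for enlarging the trial, and the fixed test uses neither.

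**What to change.** Make the primary analysis a Cochran-Mantel-Haenszel test with a common risk difference and its confidence interval, stratified by baseline rhythm and hospital. Use three rhythm groups: third degree block, second degree block, and other. The third group is needed because bradycardia and low systolic pressure also qualify a patient for entry. Keep the unadjusted chi-squared test as a sensitivity analysis. Report the effect within third degree block with a test of interaction, which serves the stated purpose of the enlargement.

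The hospital factor presumes the two hospitals named under Sample size. The Abstract refers to a single tertiary hospital, so the two statements should be reconciled.

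The cost is wording and slightly more analysis work. Baseline rhythm is already recorded for eligibility. The main downside is that some strata may be sparse, since the mix of grades is not known. A rule fixed in advance should say when the hospital factor is dropped.

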## Abstract

**Background:**

Cardiac toxicity due to ingestion of oleander plant seeds in Sri Lanka and some other South Asian countries is very common. At present symptomatic oleander seed poisoning carries a mortality of 10% in Sri Lanka and treatment of yellow oleander poisoning is limited to gastric decontamination and atropine administration. The only proven effective antidote is digoxin antibodies but these are not available for routine use because of the high cost. The main objective of this study is to investigate the effectiveness of a new and inexpensive antidote for patients with life threatening arrhythmias due oleander poisoning.

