### Outcomes

The primary outcome of this study is the reversion to sustained sinus rhythm with a heart rate >50 bpm within 2 hours of completion of bolus.

Secondary outcomes include:

1. Death

2. Change from baseline serum potassium on the 6, 12, 18 and 24 hour blood samples.

3. Time to revert and duration of reversion to sinus rhythm on the Holter monitor over the first 24 hours (reflecting the efficacy of bolus and infusion)

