### Independent data monitoring and ethics committee (IDMEC)

The IDMEC will conduct the interim analysis and examine primary and secondary outcomes.

We intend to do a planned interim analysis once a total of 120 patients had been randomised (i.e. 60 in the treatment arm and 60 in placebo) which may lead to modification of or cessation of the trial as outlined below. The IDMEC will be asked specifically to comment on the need for subsequent modification of the trial protocol for the infusion. An infusion rate modification should be recommended if there is strong evidence of a response to the bolus which is not sustained by the infusion. An interim analysis at this stage will also be used to stop the trial if there is very strong evidence for efficacy. We have a 95% power to detect a 60% treatment effect over the expected placebo response of 15% without any loss of power for the overall study (α = 0.001, β = 0.95, missing data/dropouts 10%). If such a major response is noted the IDMEC will instruct the trial team to stop the trial.

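### Kaplan-Meier curves of cumulative reversion will overstate the proportion reverting by 24 h if deaths are censored; cumulative incidence curves should replace them

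*Protocol article*

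**What the plan says.** The Statistical Analysis section of the protocol article plans three analyses of reversion:

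- The primary outcome is a proportion: "The Primary outcome (proportion with reversion to sinus rhythm) will be compared with the chi-squared test".
- For the time course, "Kaplan Meier curves will be constructed to demonstrate the cumulative reversion to sinus rhythm over time".
- For a test over time, "A Cox proportional hazard model will be used to test the overall difference in reversion to sinus rhythm between treatments", with baseline adjustment where needed.

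The Outcomes section lists death as a secondary outcome, and separately "Time to revert and duration of reversion to sinus rhythm on the Holter monitor over the first 24 hours". No analysis method is given for the duration part. Nothing says how a patient who dies before reverting enters the curves or the Cox model. The Randomisation section commits to intention-to-treat: "the analysis will include all randomised patients in the groups to which they were assigned, regardless of non-compliance, protocol deviations, withdrawal". On mortality, the Abstract says: "At present symptomatic oleander seed poisoning carries a mortality of 10% in Sri Lanka".

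**The concern.** The curves are meant to show what proportion of patients have reverted by each time. Kaplan-Meier estimates that proportion only if patients who leave the risk set early could still revert later at the same rate as those who remain. A patient who has died cannot. Censoring at death in effect shares that patient's probability among those still at risk, so the curve answers a hypothetical question (reversion if nobody died) and runs above the observed proportion. Mortality here is not negligible, and entry requires second- or third-degree block, marked bradycardia or low systolic pressure. If the arms differ in mortality, the overstatement differs too, and the gap between the two curves is no longer the gap in reversion.

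Duration of reversion has a related difficulty. It is undefined in a patient who never reverts. A comparison among reverters only would set two groups selected after randomisation against each other.

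**Working it through.** **Figure to reproduce.** The protocol gives none for the Kaplan-Meier, Cox or duration analyses. Its sample-size figures concern the two-hour proportion.

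**Inputs.**
- From the documents: mortality 10% (Abstract), not split by time, by arm, or into deaths before and after reversion; a 24 h window for time to reversion (Outcomes); 240 patients (Sample size).
- Assumed: true reversion by 24 h, *r*, of 50% to 80%; death before reversion within 24 h, *d*, of 2% to 15%; constant hazards for both events.

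**Formula.** The total cumulative hazard over 24 h is −ln(1 − r − d). Reversion's share of it is r/(r + d). With deaths censored,

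1 − KM = 1 − exp{ln(1 − r − d) × r/(r + d)}.

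**Worked case, r = 60%, d = 10%.** −ln(0.30) = 1.204; share 0.60/0.70 = 0.857; product 1.032; 1 − exp(−1.032) = 64.4%. The excess is 4.4 points. Likewise a true 56% reads as 60.0%: −ln(0.34) = 1.079; share 0.56/0.66 = 0.848; product 0.915.

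**Excess of 1 − KM over true reversion at 24 h, in percentage points:**

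| True reversion | 2% die first | 5% | 10% | 15% |
|---|---|---|---|---|
| 50% | 0.6 | 1.6 | 3.4 | 5.4 |
| 60% | 0.8 | 2.1 | 4.4 | 7.0 |
| 70% | 1.0 | 2.6 | 5.5 | 9.0 |
| 80% | 1.2 | 3.2 | 7.1 | 12.0 |

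**Check on the remedy.** In 200,000 simulated patients (r = 60%, d = 10%), Kaplan-Meier with deaths censored gave 64.5%. Keeping the dead in the risk set as unreverted to 24 h gave 60.1%, equal to the proportion that reverted.

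**Check on never-reverters.** With d = 0 the share is 1 and the formula gives 1 − (1 − r) = r. Simulation agrees (59.9% against 59.9%). Censoring living, unreverted patients at 24 h is harmless.

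**Unequal mortality, true reversion 60% in both arms.**
- Deaths first 10% in each arm: 64.4% and 64.4%, cause-specific hazard ratio 1.00.
- Deaths first 10% control, 5% active: 64.4% and 62.1%. In the active arm the total hazard is −ln(0.35) = 1.050 and the share 0.923, product 0.969; the hazard ratio is 0.969/1.032 = 0.94.
- Deaths first 10% control, 20% active: 64.4% and 70.1%, hazard ratio 1.17.

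**Early in follow-up.** With an extreme 10% dead by two hours, 15% reversion would read as 15.9% and 40% as 42.6%. The bias builds up towards 24 h.

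**Duration, invented numbers to show the mechanism.** Suppose 50% of controls revert, with a mean of 14 h. On active treatment the same 50% average 16 h, and a further 20%, sicker, average 6 h. Among reverters only: 14 h against (0.5 × 16 + 0.2 × 6)/0.7 = 13.1 h. Over all randomised patients with zeros: 0.5 × 14 = 7.0 h against 0.5 × 16 + 0.2 × 6 = 9.2 h.

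**The case against.** **Censoring at death is inferred.** The article does not say that deaths will be censored. Carrying them forward as unreverted is compatible with its wording and removes the bias. It promises to analyse everyone randomised, and censoring rules often sit in an analysis plan. This has weight, and it is why the point is conditional. It does not dispose of the point. The protocol names the estimator and what it is to display, and the usual use of that estimator does not give that quantity when death intervenes. Intention-to-treat does not settle it either, because a patient censored at death has still been included.

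**The Cox model is legitimate.** This stands. With deaths censored it compares reversion rates among patients alive and not yet reverted. Making a subdistribution model the main test would be a preference. The Cox result only needs to be labelled for what it is.

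**The consequence is limited.** This also stands. The curves are secondary, death is reported as its own outcome, and the primary comparison does not use them.

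Some stronger readings are tempting but unsupported:

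- *That patients who never revert are lost and inflate the curves.* They are validly censored at 24 h. The difficulty with non-reverters arises only for duration.
- *That the analysis will favour the wrong arm.* The documents give no mortality by arm. With equal mortality and equal reversion there is no tilt. In the constant-hazard model, a reversed ordering needs a large mortality gap with nearly equal reversion: 60% against 58% reverting with 10% against 20% dying first gives a hazard ratio of 1.09, but with 10% against 15% it is only 1.008. A hazard ratio of 0.94 is also small beside its uncertainty: with 240 × 60% = 144 reversions the standard error of the log hazard ratio is about 2/√144 = 0.17, against |ln 0.94| = 0.06.
- *That the committee's infusion decision rests on duration among reverters.* The IDMEC section asks for "strong evidence of a response to the bolus which is not sustained by the infusion" and names no measure.
- *That a reverters-only comparison of duration is planned.* No method is given, so this is a risk to close off and not a stated error.

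**Conclusion.** The point holds for the Kaplan-Meier display. If deaths before reversion are censored in the standard way, the curves overstate the proportion reverting by 24 h by about 3 to 7 points when 10% die first and 50% to 80% revert. Over the wider range of 2% to 15% dying first, the excess runs from 0.6 to 12.0 points. These sizes rest on constant hazards, on an assumed 24 h reversion rate, and on applying the 10% mortality figure to deaths before reversion within 24 h; deaths after reversion or after 24 h would reduce it. The overstatement differs between arms if mortality does, but the documents do not support a claim about which arm would gain. The Cox model is sound as a rate comparison. The chi-squared primary analysis is unaffected provided that deaths before reversion count as non-reversion. Duration needs a definition that covers every randomised patient before it can be compared between arms.

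**What to change.** 1. Replace the Kaplan-Meier curves with cumulative incidence curves of reversion over 24 h that treat death before reversion as a competing event. If every patient is observed to 24 h or death, this equals keeping those who die as unreverted to 24 h.
2. Keep the Cox model, label it a cause-specific comparison of reversion rates, and read it beside the cumulative incidence curves and the death results.
3. Make the between-arm comparison of duration on hours in sinus rhythm over the first 24 h in all randomised patients, with zero for non-reverters and for time after death. This measure combines failure to revert with loss of response, so it does not by itself show whether a response was sustained. Duration among reverters can still be described, without a between-arm test.
4. State that death before reversion counts as non-reversion in the primary outcome.

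The changes use Holter and death data already planned and leave the sample size alone. The cost is slightly more analysis work and a slightly lower displayed reversion proportion.

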### Independent data monitoring and ethics committee (IDMEC)

The IDMEC will conduct the interim analysis and examine primary and secondary outcomes.

We intend to do a planned interim analysis once a total of 120 patients had been randomised (i.e. 60 in the treatment arm and 60 in placebo) which may lead to modification of or cessation of the trial as outlined below. The IDMEC will be asked specifically to comment on the need for subsequent modification of the trial protocol for the infusion. An infusion rate modification should be recommended if there is strong evidence of a response to the bolus which is not sustained by the infusion. An interim analysis at this stage will also be used to stop the trial if there is very strong evidence for efficacy. We have a 95% power to detect a 60% treatment effect over the expected placebo response of 15% without any loss of power for the overall study (α = 0.001, β = 0.95, missing data/dropouts 10%). If such a major response is noted the IDMEC will instruct the trial team to stop the trial.

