These theoretical benefits of FDP have been shown in an animal study done at the Mississippi School of Medicine, USA. This study showed evidence of effectiveness of FDP in dogs poisoned with a relative of the yellow oleander - the common or pink oleander. Cardiac arrhythmias in dogs (6/6;100%) treated with FDP (50mg/kg IV) reverted back to sinus rhythm within 30 minutes while the arrhythmias in the control animals killed one animal and did not revert over four hours in the other five at which time they were sacrificed [7]. There was also no rise in serum potassium in the group receiving FDP while marked hyperkalemia occurred in the control group [7].

We conducted a small phase II study of increasing IV bolus doses (30 to 250mg/kg) of FDP in patients with yellow oleander poisoning in Sri Lanka in 2006-7. The aim of that study was to find a safe dose of FDP that might be used to reverse cardio-toxicity. The agent was well tolerated with no evidence of any adverse effects attributable to FDP at any of the doses and an apparent reduction of around 0.5 mmol/L of potassium and 0.3mmol/L of calcium in the highest FDP dose group. All these doses were well within the range of doses used in previous human studies for other conditions [9].

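### The interim efficacy stop is mandatory on 2-hour rhythm reversion alone and gives the deaths that the IDMEC reviews no role in the decision

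*Protocol article*

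**What the plan says.** All of the following is in the protocol article.

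- **IDMEC section, scope.** The committee runs the interim analysis and looks at both primary and secondary outcomes. The look comes after 120 randomised patients, 60 per arm, and is one "which may lead to modification of or cessation of the trial as outlined below".
- **IDMEC section, actions.** Two follow. The infusion may be modified if a bolus response is not sustained. The trial may also stop early: "An interim analysis at this stage will also be used to stop the trial if there is very strong evidence for efficacy". The efficacy stop is sized on 60% against an expected placebo response of 15%, at α = 0.001 with 10% missing data or dropout. The section ends: "If such a major response is noted the IDMEC will instruct the trial team to stop the trial".
- **Outcomes section.** The primary outcome is sustained sinus rhythm with a heart rate above 50 bpm within 2 hours of the end of the bolus. Death is the first secondary outcome.
- **Sample size section.** Spontaneous reversion by two hours is put at up to 15%. The section also states: "Second degree and third degree heart block are markers of toxicity but may not be strong predictors of death", since death may come from myocardial toxicity. It then argues that 40% reversion on FDP would probably be strong evidence of a mortality benefit.

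**The concern.** The 15% placebo response in the stopping paragraph is the spontaneous reversion rate from the Sample size section, so the response that triggers the stop is a rhythm figure read within 2 hours of the bolus. The instruction attached to it is unconditional.

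The section therefore does two things that do not meet. It asks the committee to look at deaths, and it prescribes a stop that does not depend on what the committee finds there. The protocol itself names a reason why rhythm and death may part company, so the case where they disagree is the one where the rule needs to say something. An early stop also gives up the second half of the mortality data, which could help test the hoped-for link between reversion and survival.

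**Working it through.** **1. What the trigger is.** Inputs from the IDMEC section: 15% v 60%, α = 0.001, 60 per arm, 10% loss, so 54 evaluable per arm. I take α as two-sided (z = 3.291); the article does not state sidedness. With pooled variance,

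power = Φ{ [Δ√n − z√(2p̄(1−p̄))] / √(p₁(1−p₁) + p₂(1−p₂)) }

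where Δ = 0.45, p̄ = 0.375, √(2 × 0.375 × 0.625) = 0.6847 and √(0.15 × 0.85 + 0.60 × 0.40) = 0.6062.

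- n = 54: (3.307 − 3.291 × 0.6847)/0.6062 = 1.739, power 95.9%.
- n = 60: (3.486 − 2.253)/0.6062 = 2.034, power 97.9%.

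The stated 95% reproduces when the 60% is read as the FDP response rate. Read as 15 + 60 = 75%, power exceeds 99.9%; read as a 60% relative rise to 24%, it is 1.7% (both with 54 evaluable). The trigger is thus a reversion rate, with no mortality term in it. If the boundary is applied as p < 0.001 rather than as an observed 60%, 26/60 v 9/60 (43% v 15%) already crosses it: z = 3.41, p = 0.0006.

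**2. What a condition on deaths would face at the look.** Assumptions: 60 per arm; 10% mortality on placebo, the article's figure for symptomatic poisoning, with 5% to 20% as a range because the rate in enrolled patients is not given; deaths independent of reversion. Deaths per arm are binomial(60, p), and the probabilities below come from exact enumeration of the two arms.

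| Placebo mortality | FDP mortality | P(any excess on FDP) | P(excess of 5 or more) |
|---|---|---|---|
| 10% | 5% | 11% | 0.4% |
| 10% | 10% | 44% | 8% |
| 10% | 20% | 92% | 65% |
| 5% | 5% | 42% | 3% |
| 20% | 20% | 45% | 15% |

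**3. Effect on the chance of an early stop.** Take true reversion of 60% v 15%, equal 10% mortality and 60 per arm:

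- rule as written: 97.9%;
- barred by any excess of FDP deaths: 0.979 × (1 − 0.439) = 55%;
- barred only by an excess of 5 or more: 0.979 × (1 − 0.084) = 90%.

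**4. Why a significance test on deaths is not the answer.** A two-sided 0.05 test of 20% v 10% has 33% power at 60 per arm (58% at 120), so it misses a doubling about two times in three. Twelve deaths against 6 gives Fisher p = 0.20.

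**5. How much mortality information is at stake.** The 95% CI for the risk ratio is exp(±1.96 √(2/d − 2/n)), with d deaths among n patients in each arm. For 6 v 6 of 60 it is 0.34 to 2.93; for 12 v 12 of 120 it is 0.47 to 2.14.

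**The case against.** **The committee sees the deaths.** This is correct. An independent committee that examines secondary outcomes would not act in ignorance of them. But the closing sentence gives it no discretion, so the review and the instruction still need to be reconciled.

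**Stopping on the primary outcome at α = 0.001 is conventional.** True, and the threshold is not in dispute. The point concerns only the unconditional wording.

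**The sentence on heart block concerns block as a predictor of death, not reversion produced by treatment.** A fair distinction. The same section also expects 40% reversion to carry over to mortality, and the stop is sized on 60%. The sentence does not show that reversion is a poor surrogate; it shows that the protocol treats the link as uncertain.

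**Early deaths may already count against FDP.** Under intention to treat, a death before reversion would plausibly be a non-response. The article does not say so, and later deaths would still carry no weight in the rule.

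**Even 240 patients would not settle mortality.** True, as the intervals show. That argues against a formal test of deaths, not against a consistency check.

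Three stronger readings are tempting, and the document does not support them.

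- *FDP could be declared effective while deaths run against it.* The text says only that the trial stops.
- *The plan lacks a harm boundary or enough looks at deaths.* A condensed article commonly leaves these to the full protocol or the committee's charter, so their absence here is no finding.
- *Harm is to be expected because experience in this poisoning is one small bolus study.* The Background reports no adverse effects attributable to FDP in that study. It also reports safe use elsewhere of 750 mg/kg cumulatively over 12 hours. Bolus plus infusion here totals 250 + 6 × 24 = 394 mg/kg, or 644 mg/kg with a second bolus.

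**Conclusion.** The point holds in a narrow form. The printed rule requires an efficacy stop on 2-hour rhythm reversion and assigns the deaths no part in that decision, although the committee reviews them and the protocol doubts that block strongly predicts death. This is a defect in a stated rule, not an omission.

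The practical size depends on the true mortality effect, which is unknown. If FDP doubled mortality from 10% to 20%, an excess of at least 5 deaths would be present at the look in 65% of trials, and the rule would still order a stop wherever reversion met the trigger. Doubling is an illustration; nothing in the document suggests it. The figures rest on 60 per arm, 10% placebo mortality and deaths independent of reversion. The repair is worth making because it is cheap, provided it tolerates small chance imbalances.

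**What to change.** Replace the last sentence of the IDMEC section with wording such as:

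> If the reversion criterion is met, and the IDMEC's review of deaths by arm does not point materially against FDP, the IDMEC will recommend stopping the trial; otherwise it will advise on continuation on the totality of the data.

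This connects the stop to the review that the section already requires. Do not define the condition as no numerical excess of FDP deaths: that would withhold 44% of efficacy stops by chance when mortality is equal at 10%. If the committee wants a guide figure, an excess of about 5 deaths would withhold 8% in that case (3% at 5% mortality, 15% at 20%). It should inform judgement rather than bind it.

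The cost is one sentence and a somewhat lower chance of an early stop, from about 98% to about 90% under the assumptions above with the guide figure of 5. No efficacy alpha is spent, because the condition can only make an efficacy stop less likely.
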